### 2.5. Interventions

All patients with PD underwent PA or MA therapy twice a week for 8 weeks. Conventional treatments, including L-DOPA, catechol-O-methyl transferase inhibitor, monoamine oxidase inhibitor, and dopamine agonist treatments, were allowed during the trial. For combination drugs, any drugs taken four weeks before participation in the study were allowed at the discretion of the researcher if they were not prohibited drugs (steroids, immunosuppressants, neuropsychiatric drugs) or other drugs that might have affected the results of the study. Analgesic drugs could be continuously taken if the dose had been stable for more than two weeks at the time of screening, but the details of drug administration (name of the drug, purpose of administration, dosage, and duration of administration) were recorded at each visit. In addition, any oriental medical therapy to improve PD pain, other than the intervention being performed in this study, was prohibited. Drugs that could affect symptoms during the period of clinical research were prohibited from being administered at the judgment of the researchers. Procedures, including details of needling (i.e., acupoints centered on the area where the participant complains of pain, needle stimulation, and retention time) to be administered in the PA and MA groups, were performed according to the clinical judgment of a senior Korean medicine doctor with more than 10 years of clinical experience based on the patient’s condition in the pragmatic randomized controlled trial (RCT). All procedural methods were retrospectively recorded. Treatment was discontinued based on the withdrawal of consent by participants or their legal representatives, violation of the eligibility criteria during the clinical trial, occurrence of adverse events (AEs), or poor compliance defined as receiving less than five of the sixteen total treatments.

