### 2.10. Safety Assessment and AEs

A clinical laboratory examination was performed at baseline, before treatment, and 8 weeks after completing treatment (visit 18) as a safety assessment for all participants. All AEs, defined as undesirable and/or unexpected medical findings that were absent prior to commencing this clinical trial, were recorded. AEs were reported to the institutional review board (IRB) of Kyung Hee University Hospital at Gangdong, which determined whether the trial should be discontinued. The causal link between AEs and the procedure was categorized into six stages as determined by the research clinician: Definitely related, Probably related, Possibly related, Probably not related, Definitely not related, and Unknown. Appropriate treatment and follow-up were provided for severe AEs (SAEs).

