	NRS			O	O	O		O
	UPDRS II, III			O	O	O		O
	Pain catastrophizing score			O		O		
	EQ-5D			O		O		
	PDSS-2			O		O		
	Facial expression analysis			O		O		
	Syndrome differentiation		O				O	
	BDI II		O				O	
	BAI		O				O	
	Gait analysis			O		O		O
MRI measurement			O				O	
Blood collection for molecular analysis		O				O		
PA or MA or UC				O (every visit)	O (every visit)	O		
Treatment compliance						O		
Identification of concomitant drug change		O	O	O (every visit)	O (every visit)	O	O	O
Identification of adverse reaction(s)					O (every visit)	O	O	O

MRI, magnetic resonance imaging; KPPS, King’s Parkinson’s Disease Pain Scale; NRS, numerical rating scale; UPDRS, Unified Parkinson’s Disease Rating Scale; EQ-5D, Euro-Quality of Life-5 Dimension; PDSS, Parkinson’s Disease Sleep Scale; BDI, Beck Depression Inventory; BAI, Beck Anxiety Inventory; PA, pharmacopuncture; MA, manual acupuncture; UC, usual care

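### Table 2 starts the adverse-reaction check later than treatment, against section 2.10, and the AE definition leaves out worsening of existing conditions

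*Protocol article*

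**What the plan says.** **Schedule.** Table 2 has a row for "Identification of adverse reaction(s)". It is empty under visits 1, 2 and 3, carries an every-visit mark under visit 10, and is marked at visits 18, 19 and 20. The treatment row (PA, MA or UC), the vital-signs row and the row "Identification of concomitant drug change" each carry an every-visit mark under both visit 3 and visit 10. Visit 3 is labelled as baseline and placed in week 1.

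**Text.** Section 2.10 states: "All AEs, defined as undesirable and/or unexpected medical findings that were absent prior to commencing this clinical trial, were recorded". It names no visit at which recording starts. It also provides for a causality rating of AEs in six categories, and section 2.11.2 has AEs classified by study group.

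**Treatment course.** Section 2.5: "All patients with PD underwent PA or MA therapy twice a week for 8 weeks". The same section defines poor compliance as "receiving less than five of the sixteen total treatments".

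**Laboratory tests.** Section 2.10 puts the second safety laboratory test at "8 weeks after completing treatment (visit 18) as a safety assessment for all participants". Table 2 shows laboratory tests at visits 1 and 18, with visit 18 in week 8.

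**The concern.** Safety stands beside effectiveness in the first aim (section 2.1). The test product is an injected herbal extract, and Table 1 excludes patients with earlier hypersensitivity to PA, so the authors themselves foresee reactions to it. A schedule with no adverse-reaction check in the column where exposure starts is thin at the point where such reactions would first be looked for. Site staff tend to work from the schedule table, so what the table leaves blank may not be asked.

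The definition is a separate problem. Every patient enters with PD and with a KPPS score above 0 (Table 1). In such a population, harm can take the form of a symptom that was already there and gets worse. A rule that requires the finding to have been absent before the trial does not clearly admit this. The sentence that all AEs are recorded cannot repair it, because "all" reaches only as far as the definition.

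AEs also feed other decisions: stopping of treatment (section 2.5), the ethics board's decision on whether the trial continues (section 2.10), and the independent committee's review (section 2.12). Each depends on when AEs are sought and on what counts as one.

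**Working it through.** **1. Map visits to sessions.** Inputs: two sessions per week for 8 weeks (section 2.5); baseline and first treatment at visit 3, last treatment mark at visit 18 (Table 2).

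- Sessions from the text: 2 × 8 = 16, the total given in section 2.5.
- Sessions from the table: visits 3 to 18 inclusive = 18 − 3 + 1 = 16. The two agree.
- Visit v is session v − 2. Visit 10 is session 8, the second of week 4. Visit 18 is session 16, the second of week 8. Both match the week labels in Table 2.

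**2. Compare the rows of Table 2.**

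| Row | Visit 3 | Visit 10 | Visit 18 | Visit 19 | Visit 20 |
|---|---|---|---|---|---|
| PA, MA or UC | every visit | every visit | yes | – | – |
| Vital signs | every visit | every visit | yes | yes | yes |
| Concomitant drug change | every visit | every visit | yes | yes | yes |
| Adverse reactions | blank | every visit | yes | yes | yes |

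The adverse-reaction row has the same number of cells as the others and its entries run to the last column, so the blank is not a shifted row.

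**3. Count sessions without a scheduled check.**

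- Strict reading: the visit-3 column stands for visits 3 to 9 and the visit-10 column for visits 10 to 17, as the paired marks in the other rows suggest. Unchecked visits: 9 − 3 + 1 = 7, and 7/16 = 43.75%, about 44%. A reaction at visit 3 would first be asked about seven visits later, at two visits per week 7/2 = 3.5 weeks.
- Lenient reading: the mark under visit 10 means every visit after baseline. Unchecked: visit 3 only, and 1/16 = 6.25%, about 6%. A reaction at visit 3 would be asked about at visit 4.
- With an every-visit mark added under visit 3: 0 of 16.

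**4. Test the definition.** The qualifying condition is that the finding was absent before the trial. A patient whose existing pain, rigidity or low mood becomes worse has a finding that was present. Read literally, it is not an AE. Where would it show? KPPS, NRS and UPDRS II and III are scheduled at visits 3, 10, 18 and 20 (KPPS also at visit 1); the depression and anxiety inventories at visits 2 and 19. These are efficacy measures. They receive no causality rating and do not enter the AE classification by group.

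**5. Check the laboratory timing.** Treatment ends at visit 18, week 8. Eight weeks after that is week 8 + 8 = 16. The last visit is visit 20 at week 12, so no scheduled visit fits the sentence as worded. Visit 18 and week 8 do fit each other, which points to a test 8 weeks after the start of treatment.

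**The case against.** The strongest reply is that section 2.10 has all AEs recorded from no stated start visit, that AEs are a ground for stopping treatment, and that an independent committee monitors safety regularly. On that view the blank cell is an inconsistency in a table, and nothing shows that an event was lost. This stands. A reader might infer that early reactions are missed, or that the first injection is unmonitored; the documents support neither. Vital signs and drug changes are marked at visit 3, the text requires recording, and a later check can still bring out an earlier event.

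The blank also has an innocent reading. Visit 3 is the baseline visit, and a question put before the first session has nothing to ask about. That explains one cell, and it is why the lower figure of 1 of 16 has to be given beside 7 of 16. It does not make the table clear, since the other rows use an every-visit mark in both columns.

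On the definition, it can be said that a clinically worse state is itself a new undesirable finding, that a condensed article need not give full AE rules, and that the named symptoms are measured in any case. The first argument shows that the sentence can be stretched; two assessors could then classify the same event differently. The second would excuse silence, but here a rule is stated, and stated narrowly. The third is right that worsening would not be invisible, and it limits the consequence to the AE record.

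A reader might also infer that AE rates would be too low chiefly in the PA and MA arms. The documents give no figure for this, and both the blank and the definition apply to all three arms.

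**Conclusion.** The point holds as a contradiction between Table 2 and section 2.10 together with an AE definition that is too narrow for this population. It should be corrected. The schedule gap is 1 of 16 sessions on the lenient reading and 7 of 16 on the strict one. The documents do not settle which is meant. These are counts of sessions without a scheduled check, not estimates of AEs lost; the supportable consequence is that early reactions may be under-recorded or rest on recall. The count assumes that visits 3 to 18 are the sixteen sessions, which the text and the table both bear out.

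The definition is the firmer half, because no other sentence in the article offsets it. Its effect on AE numbers cannot be sized from the documents, and no difference between arms is shown.

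The laboratory sentence is a minor wording error. It might suggest a lost or impossible safety sample, but its own reference to visit 18 agrees with Table 2, so no sample is in doubt.

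**What to change.** 1. In Table 2, mark adverse-reaction identification at every visit from visit 3 through visit 20, so that the schedule agrees with section 2.10. If the visit-3 question is meant to follow the session, a footnote can say so.
2. In section 2.10, define an AE as any untoward finding that is new, or worse than before the first session, and state that this applies in all three arms.
3. In section 2.10, reword the timing of the second laboratory test to agree with Table 2, where visit 18 is week 8 and the last treatment visit.

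The cost is one table row and two sentences. Table 2 already schedules these visits for PA, MA and UC, so the added burden is a brief question at each. No sample-size or efficacy analysis is affected. If data have already been collected under the printed schedule, the report should state at which visits AEs were actively sought and whether worsening of existing conditions was recorded as an AE.

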## Data Availability

The source document data for the clinical trials were deposited in the Clinical Trial Center of Kyung Hee University Hospital at Gangdong repository after completion of this study (KHNMCOH 2022-02-005-001).
